#### Implementation {16c}

Following participant consent to participate in the study, the coordinator will access the computer-generated randomization file to discover which treatment arm the participant has been randomized to. The participant and the referring sleep medicine provider will be informed of the randomization outcome. For participants randomized to ICAU, the coordinator will facilitate the scheduling of an appointment at the sleep clinic for ICAU through the referring site’s standard operating procedures. For participants randomized to the digital CBTI hub, the coordinator will facilitate a warm hand-off to the clinician affiliated with the digital CBTI hub, and the participant will then initiate CBTI under their close supervision.

### Assignment of interventions: blinding

#### Who will be blinded {17a}

Given the nature of the study design, blinding of participants or clinicians will not be possible. However, masked data will be provided to the biostatistician who will perform the analyses. Randomization will be unmasked only after analyses are finalized. Furthermore, clinicians providing ICAU or treatment via digital CBTI hubs will not participate in periodic interim analyses of the primary and secondary outcomes to avoid biases and/or changes in practice over the course of the study.

#### Procedure for unblinding if needed {17b}

Not applicable: neither enrolled patients nor clinicians will be blinded in this trial.

### Data collection and management

#### Plans for assessment and collection of outcomes {18a}

Participant data will be collected via HIPAA-compliant electronic data capture, including the NOCTEM COAST patient app. For all assessments on the app, validation checks are in place to ensure data quality and completeness. The research coordinators are trained on the use and functionality of the COAST patient app and will be available to participants should questions arise about using the technology to complete the assessments. Additional information about the study questionnaires can be found in the above section titled Outcomes.

#### Plans to promote participant retention and complete follow-up {18b}

The retention of participants for the follow-up period can be challenging. We will employ strategies that allowed us to complete post-intervention procedures and achieve high levels of adherence (> 80%) in previous studies, including, for example, participation gratitude letters [53–55].

#### Data management {19}

No hard copy data will be collected for this study. All participant information and assessments will be collected via HIPAA-compliant electronic data capture, including the COAST patient app. Security and confidentiality in a mobile health application are of paramount importance, and layered security measures are used to protect the privacy and confidentiality of the research data from the participants.

#### Confidentiality {27}

To protect confidentiality, each participant will have a research identification (ID) consisting of a 6-digit alpha-numeric code that will be used in lieu of personally identifiable information (name, date of birth, Social Security number, etc.) for data collection and storage. The research ID numbers are unrelated to any potentially identifiable numerical series, such as social security number, medical record number, or date of birth. Participant name and contact information will be collected for the purposes of contacting participants during study procedures. This information will be stored only for the duration of the study, stored separately from the study data, and deleted at the completion of the study. Study data will be kept strictly confidential, and participants’ identities will not be revealed in any publication. All data gathered in this project will be completed electronically, and data will be saved automatically into the main database. The AWS GovCloud managed by NOCTEM are cloud-based databases that are protected by several procedures, including password protection of participant data and a firewall.

#### Plans for collection, laboratory evaluation, and storage of biological specimens for genetic or molecular analysis in this trial/future use {33}

Not applicable: no biological specimens will be collected in this trial.

## Statistical methods

### Statistical methods for primary and secondary outcomes {20a}

Preliminary data analyses will be performed prior to testing the aims to check for collinearity of covariate and outcome measures, to ensure completeness and accuracy of data, and to evaluate distributions. The primary and secondary aims will be tested with non-inferiority hypotheses of the general form: H0: digital CBTI hubs are inferior to ICAU versus H1: digital CBTI hubs are non-inferior ICAU. For each outcome, we will calculate the standardized differences (Cohen’s *d*) as digital CBTI hubs—ICAU, such that a positive difference is in favor of ICAU if higher values are worse, and a negative difference is in favor of ICAU if higher values are better. Since higher values indicate worse outcomes for our measures of interest (e.g., ISI, depression, anxiety), we will use a non-inferiority margin (NIM) of 0.50 and declare digital CBTI hubs to be non-inferior to ICAU if the upper bound of the 95% confidence interval (CI) for *d* is ≥ 0.50. We will declare digital CBTI hubs to be inferior to ICAU if the upper bound of the 95% CI for *d* is ≤  − 0.50. For example, if *d* (95% CI) = 0.10 (− 0.20, 0.40), we would declare digital CBTI hubs as non-inferior to ICAU because 0.40 < 0.50. But if *d* (95% CI) = 0.40 (0.10, 0.70), we would declare digital CBTI hubs to be inferior because − 0.70 ≥ 0.50. These one-sided decision rules equate to requiring the effect size comparing digital CBTI hubs to ICAU to have no more than moderate strength (|*d*|= 0. 5) in favor of ICAU.

Our primary strategy will compare digital CBTI hubs and ICAU using analyses that are straightforward and highly interpretable while still accounting for other important covariates. We will use analysis of covariance (ANCOVA) to determine whether ISI at 6–8 weeks and at 3-month follow-up differs between digital CBTI hubs and ICAU after controlling for baseline ISI and other relevant covariates. Cohen’s *d* effect sizes (*d* ESs) with 95% CIs estimated from the ANCOVA model will be calculated and compared to the NIM as outlined above. To examine more nuanced effects across time, we will calculate the rate of change in ISI symptoms (ΔISI) across baseline, 6–8 weeks, and 3-month follow-up for each individual and then use linear regression to compare ΔISI between digital CBTI hubs and ICAU after controlling for relevant covariates. We will also model the repeatedly measured outcome using mixed effects models with a random intercept and slope. Cohen’s *d* ESs and 95% CIs estimated from these models will be calculated and compared to the NIM as outlined above.

For non-inferiority tests, we set an allowable one-sided type I error rate of *α* = 0.025. Conservatively adjusting for our two a priori *t*-tests (6–8 weeks and 3-month follow-up), we use *α** = 0.0125 to determine power. Our full sample size of 94 per group will provide 0.88 power. However, even with attrition of 25% (*N* = 70 completers per group), we expect to have 0.80 power. We will use the same statistical approach to assess and compare changes in depression and anxiety symptom severity at 6–8 weeks and at 3-month follow-up.

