### Objectives {7}

The overall objective of this trial is to evaluate the impact and acceptability of digital CBTI hubs to augment military treatment facilities’ capabilities in behavioral sleep medicine and maintain high-quality clinical outcomes. The specific aims are to (1) examine and compare the changes in insomnia severity at baseline, at 6–8 weeks, and at 3-month follow-up; (2) examine and compare the changes in daytime symptoms of depression and anxiety at baseline, at 6–8 weeks, and at 3-month follow-up; and (3) examine and compare patient satisfaction with ICAU versus CBTI via a digital CBTI hub.

The first hypothesis is that improvements in insomnia symptom severity in service members with a diagnosis of chronic insomnia following remote, asynchronous delivery of CBTI via a digital CBTI hub will be non-inferior to improvements detected following ICAU after 6–8 weeks and at 3-month follow-up. The second hypothesis is that improvements in daytime symptoms of depression and anxiety in service members with a diagnosis of chronic insomnia following remote, asynchronous delivery of CBTI via a digital CBTI hub will be non-inferior to improvements detected following ICAU after 6–8 weeks and at 3-month follow-up. The third hypothesis is that satisfaction with insomnia care following treatment through a digital CBTI hub will be non-inferior to ICAU.

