Satisfaction with insomnia treatment will be assessed using two measures including an adapted version of the Insomnia Treatment Acceptability Scale (ITAS) [51] and the Client Satisfaction Questionnaire [52]. An adapted version of the ITAS will be used to assess overall perceived acceptability and treatment preferences for either of the two CBTI modalities. On the ITAS, both treatment options will be described, and participants will be asked to rate identically worded questions about the acceptability of the treatment for oneself and others, likelihood of adhering to treatment recommendations, and expectations of short- and long-term treatment effectiveness for specific insomnia symptoms (e.g., difficulty falling or staying asleep), expected impact of insomnia treatment on daytime symptoms of insomnia, and severity of expected side effects. These items are rated for both treatments, both of which are scored on a 10-point scale. The total score for each subscale is the average of the 8 items, with higher scores indicating greater willingness to utilize the treatment. Reported Cronbach’s values for the scales are greater than 0.80. For this trial, we will contrast responses to ICAU and digital CBTI hubs. The Client Satisfaction Questionnaire is an 8-item survey that assesses the perceived quality of care, services, and clinicians encountered during treatment. Higher scores indicate greater satisfaction. Both satisfaction surveys will be administered at 6–8 weeks only.

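### The printed decision rule for ISI, PHQ-2 and GAD-2 has its inequalities the wrong way round and contradicts its own worked examples; the intended direction is clear, but the operative text must be corrected

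*Protocol article*

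**What the plan says.** All of the decision rule stands in one paragraph of the Protocol article, Statistical methods for primary and secondary outcomes {20a}.

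- **Direction.** d is hub minus ICAU, "such that a positive difference is in favor of ICAU if higher values are worse". The paragraph adds that "higher values indicate worse outcomes for our measures of interest", naming ISI, depression and anxiety.
- **Margin.** "we will use a non-inferiority margin (NIM) of 0.50".
- **Rule for non-inferiority.** The plan will "declare digital CBTI hubs to be non-inferior to ICAU if the upper bound of the 95% confidence interval (CI) for *d* is ≥ 0.50".
- **Rule for inferiority.** "We will declare digital CBTI hubs to be inferior to ICAU if the upper bound of the 95% CI for *d* is ≤" −0.50.
- **Example 1.** For d = 0.10 with interval (−0.20, 0.40): "we would declare digital CBTI hubs as non-inferior to ICAU because 0.40 < 0.50".
- **Example 2.** For d = 0.40 with interval (0.10, 0.70) the hub is called inferior. The printed reason is that −0.70 is at or above 0.50.
- **Closing sentence.** The rules are said to amount to ruling out a more than moderate effect (|d| = 0.5) in ICAU's favour.

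The next paragraph of {20a} refers the ANCOVA and mixed-model effect sizes back to this rule and uses the same approach for depression and anxiety. Sample size {14} and {20a} both give 0.88 power with 94 per group at a one-sided α* of 0.0125.

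On satisfaction, the third hypothesis in Objectives {7} is that "satisfaction with insomnia care following treatment through a digital CBTI hub will be non-inferior to ICAU". Outcomes {12} says of the Client Satisfaction Questionnaire: "Higher scores indicate greater satisfaction".

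**The concern.** With d defined as hub minus ICAU and higher scores worse, a large positive d is the bad result for the hub. Non-inferiority therefore means excluding values of d at or above +0.50, which requires the upper limit to lie below +0.50. The printed rule asks for the upper limit to be at or above +0.50, so it rewards failure to exclude the margin. The printed inferiority rule has the wrong sign and uses the wrong limit: an upper limit at or below −0.50 puts the whole interval on the hub's side, beyond the margin.

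This is the only decision rule in the article, and it governs the primary outcome at both time points as well as depression and anxiety. It is also the gate for the superiority tests in Methods for additional analyses {20b}. Read literally, that gate would open only when the upper limit is at least 0.50, where superiority (upper limit below 0) is impossible. A pre-specified primary criterion that says the reverse of the hypothesis leaves room for dispute once results are known.

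**Working it through.** **Inputs.** Margin 0.50 on a standardised scale (SD = 1), 95% CI, and d = hub minus ICAU with higher worse ({20a}). 94 per group in full and 70 per group after 25% attrition ({14}, {20a}). 1:1 allocation ({16a}). One-sided α = 0.025, with α* = 0.0125 used for power. The article does not state the true d assumed for power; I take d = 0.

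**Step 1: reproduce the stated power.** SE(d) = √(2/n). For n = 94, SE = √(2/94) = 0.1459.

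Power of the rule *upper limit < 0.50* at d = 0, one-sided 0.0125:
Φ(0.50/0.1459 − 2.241) = Φ(3.428 − 2.241) = Φ(1.186) = 0.882 (0.878 by noncentral t).

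This matches the stated 0.88. The sample size was therefore computed for the opposite of the printed rule.

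**Step 2: how the printed rule behaves.** Let U = d̂ + 1.96·SE. Then P(U ≥ 0.50 | d) = 1 − Φ((0.50 − 1.96·SE − d)/SE).

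- n = 94, half-width 0.286. At d = 0: 1 − Φ((0.50 − 0.286)/0.1459) = 1 − Φ(1.468) = 0.071.
- n = 70, SE = 0.1690, half-width 0.331. At d = 0: 1 − Φ(0.998) = 0.159 (0.164 by noncentral t).
- At d = 0.50 the expression reduces to 1 − Φ(−1.96) = 0.975 for any n.

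Probability of declaring non-inferiority:

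| True d | Printed rule, 94/arm | Printed rule, 70/arm | Upper limit < 0.50, 94/arm | Upper limit < 0.50, 70/arm |
|---|---|---|---|---|
| 0 | 7.1% | 15.9% | 92.9% | 84.1% |
| 0.10 | 21.7% | 34.2% | 78.3% | 65.8% |
| 0.40 | 89.9% | 91.4% | 10.1% | 8.6% |
| 0.50 | 97.5% | 97.5% | 2.5% | 2.5% |
| 0.80 | >99.9% | >99.9% | <0.1% | <0.1% |

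At the margin, the opposite rule gives exactly the stated one-sided error of 2.5%; the printed rule gives 97.5%. The printed inferiority rule (U ≤ −0.50) has probability about 4 × 10⁻⁸ at d = 0 with 94 per arm, and reaches only 2.5% when the hub is truly better by the full margin (d = −0.50).

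**Step 3: run the article's examples through its own rule.**

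| Example | Upper limit | Article concludes | Printed rule gives | Upper limit < 0.50 gives |
|---|---|---|---|---|
| 1: (−0.20, 0.40) | 0.40 | non-inferior | neither | non-inferior |
| 2: (0.10, 0.70) | 0.70 | inferior | non-inferior | non-inferiority not shown |

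Neither conclusion follows from the printed rule. The inequality given for example 2, −0.70 ≥ 0.50, is false. The interval (0.10, 0.70) also contains values of d below the margin, so it does not establish inferiority beyond it; that would need the lower limit above +0.50.

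**The case against.** The strongest reply is that nobody would apply the rule as printed. The hypotheses, example 1, example 2's refusal to accept an upper limit of 0.70, the closing sentence and the 0.88 power all point the same way. That stands. A reader might infer from the table that the design is wrong or that the trial will reach the reverse conclusion; the article does not support this. The 97.5% and 7% show what the literal text means and do not estimate a likely outcome.

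A symbol misread in text extraction could explain one reversed inequality. It is an unlikely explanation for three slips of different kinds: the reversed sign of inequality in the first rule, the wrong region in the second, and the stray minus in example 2. An unseen SAP does not answer the point either, because nothing is missing here; the article states the rule wrongly.

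A second tempting inference is that the upper-limit rule would pass a hub that does clearly worse on satisfaction. The article does not say so. It ties the upper-limit rule to measures where higher is worse, states the mirrored sign convention for measures where higher is better, and extends the same approach by name only to depression and anxiety. What remains is that the satisfaction rule is not written out.

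The label in example 2 is a fair but secondary criticism. It follows the article's naming of the null hypothesis and does not change whether non-inferiority is declared.

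**Conclusion.** The concern holds for ISI, PHQ-2 and GAD-2: both printed decision sentences are wrong and contradict the examples beside them. Literally applied, the rule declares non-inferiority 97.5% of the time for a hub worse by the full margin, and about 7% (94 per arm) or 16% (70 per arm) of the time for an identical hub. The intended rule, upper limit below +0.50, can be recovered from the same paragraph and from the power figure, so this is an error in the operative text and not in the design. It must still be corrected, because it is the only stated criterion for the primary question.

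The figures assume a normal approximation, unit SD, equal arms and no precision gain from covariates. Such a gain would lower the 7% and 16% further and leave the 97.5% at the margin unchanged. That the 0.88 power was computed at d = 0 is my assumption; the close match supports it. For satisfaction there is a gap in wording and no reversed rule.

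**What to change.** Rewrite the decision paragraph in {20a}, before treatment codes are unmasked:

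- **ISI, PHQ-2, GAD-2** (d = hub minus ICAU): non-inferior if the upper confidence limit is < +0.50; inferior beyond the margin only if the lower limit is > +0.50; otherwise non-inferiority not shown.
- **Example 2:** not shown, because 0.70 ≥ 0.50.
- **Satisfaction scales** (higher is better), as a clarification: non-inferior if the lower limit is > −0.50.

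The rewritten rule should also state its confidence level deliberately. With 94 per arm and d = 0, a 95% interval gives power 0.929, while the stated 0.88 corresponds to a 97.5% interval (one-sided 0.0125). That choice is a separate matter from the direction of the rule.

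The cost is wording in the protocol, and in the SAP if it repeats the printed rule. Correcting the direction changes neither design, sample size nor data collection.

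### The second worked example calls the hub inferior when its interval shows only that non-inferiority was not demonstrated

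*Protocol article*

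**What the plan says.** All of the relevant text is in the Protocol article, section Statistical methods for primary and secondary outcomes {20a}.

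- The hypotheses are "H0: digital CBTI hubs are inferior to ICAU versus H1: digital CBTI hubs are non-inferior ICAU".
- The effect is the standardised difference, hub minus ICAU, so that "a positive difference is in favor of ICAU if higher values are worse". For ISI, depression and anxiety, "we will use a non-inferiority margin (NIM) of 0.50".
- The formal inferiority sentence reads "We will declare digital CBTI hubs to be inferior to ICAU if the upper bound of the 95% CI for" d is at or below −0.50. The formal non-inferiority sentence asks for an upper bound at or above 0.50, which is the reverse of what the examples do.
- First example: d = 0.10 with limits −0.20 and 0.40. Here "we would declare digital CBTI hubs as non-inferior to ICAU because 0.40 < 0.50".
- Second example: d = "0.40 (0.10, 0.70"). Here "we would declare digital CBTI hubs to be inferior because" of a comparison printed as −0.70 ≥ 0.50. The only workable reading is that the upper limit, 0.70, is at least 0.50.

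The same section then applies the comparison with the margin to ISI at 6–8 weeks and at 3-month follow-up, and uses the same approach for depression and anxiety.

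**The concern.** With inferiority as the null hypothesis, an upper limit at or above 0.50 means that the null was not rejected. The second example reports this as though the null had been established. The criterion in the first example is an upper limit below 0.50 and that in the second is an upper limit of 0.50 or more. These are exact complements, so a trial that follows the examples must end in one label or the other, and an imprecise result has nowhere to go except inferior.

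The formal inferiority sentence does not rescue the rule. An upper bound at or below −0.50 on a scale where higher is worse means that the hub is better by at least the margin. Reversing the inequality in the non-inferiority sentence alone would leave the second example and its conclusion in place.

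What is at stake is the label attached to a failed non-inferiority test on the primary outcome and on the symptom outcomes. The article wants its result to inform practice quickly. A report that the hub is inferior would be read very differently from a report that non-inferiority was not shown.

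**Working it through.** **Inputs.** Margin 0.50 in SD units, direction hub minus ICAU, 95% CI and the two worked intervals, all from {20a}. One-sided alpha 0.025, reduced to 0.0125 for the power calculation; 94 per group, or 70 completers per group after 25% attrition (Sample size {14} and {20a}). Allocation 1:1 ({16a}).

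**Reproducing the plan's power.** With SE = √(2/n), n = 94, true d = 0 and one-sided alpha 0.0125, power to show non-inferiority is 0.882 by the normal approximation and 0.878 by the noncentral t. This matches the stated 0.88. The stated 0.80 at 70 per group does not reproduce at that alpha (0.763 and 0.755), but nothing below depends on it.

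**The second example against its own interval.**
- Implied SE = (0.70 − 0.10) / (2 × 1.96) = 0.153.
- Evidence of a deficit beyond the margin: z = (0.40 − 0.50) / 0.153 = −0.65, one-sided p for d > 0.50 = 0.74.
- Evidence of non-inferiority: one-sided p = 0.26.
- Evidence of any deficit: z = 0.40 / 0.153 = 2.61, one-sided p for d > 0 = 0.004.

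The interval therefore shows ICAU better by some amount and leaves the size relative to the margin open. The estimate itself lies inside the margin.

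**The two readings of the rule side by side.**

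| Upper limit U | Worked examples | Formal sentences as printed |
|---|---|---|
| U ≤ −0.50 | non-inferior | inferior |
| −0.50 < U < 0.50 | non-inferior | no label |
| U ≥ 0.50 | inferior | non-inferior |

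The examples and the formal sentences agree in no row.

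**How often equal treatments would be called inferior under the examples' criterion.** P(U ≥ 0.50) at true d = 0 is 1 − power at one-sided 0.025, the level that matches a 95% CI.

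| n per group | Normal approximation | Noncentral t | Normal: U ≥ 0.50 and interval includes 0 |
|---|---|---|---|
| 94 | 7.1% | 1 − 0.9265 = 7.4% | 4.6% |
| 70 | 15.9% | 1 − 0.8358 = 16.4% | 13.4% |

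The half-width of the 95% CI is about 0.29 at 94 per group and 0.33 at 70, so the label begins at an estimate of about 0.21 or 0.17.

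**After the change.** If inferiority by the margin requires a lower limit at or above 0.50, equal treatments receive that label in fewer than 0.0001% of trials at either size. The second example, with lower limit 0.10, becomes non-inferiority not shown.

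**The case against.** The strongest reply is that the two-outcome rule comes from one illustration, while the formal inferiority sentence says something else. That stands in part. A reader might infer that the plan consistently labels every failed test as inferior. The document does not support this, because its formal sentences, as printed, leave upper bounds between −0.50 and 0.50 without a label. The accurate statement is that the example and the formal sentence contradict each other, and that neither is a valid test of inferiority.

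The other objections limit the size of the point:

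- The example's interval excludes 0, so a reader who took it as showing no difference between the arms would be wrong. It is unresolved only against the margin.
- The plan does not say whether inferior means worse by the margin or worse at all. If it meant a lower limit above 0, the example would qualify, but for a reason the plan does not give. The fix should report that question separately.
- At true d = 0.25 the label would appear in about 60% of trials at 94 per group and 69% at 70 (noncentral t, 95% CI). A reader might take these as the chance of condemning a hub as good as ICAU. They are not, because at d = 0.25 the hub is somewhat worse.
- The 25% attrition is a contingency in the plan. Sample size {14} names the full sample as the primary strategy.
- The primary analysis is a baseline-adjusted ANCOVA. If the baseline–outcome correlation were 0.5 and d were scaled to the unadjusted SD (neither is in the document), the rates at d = 0 would fall to about 2.4% and 7.6%.
- Rates at alpha 0.0125 would be higher, about 12% and 24%. However, the plan uses that level to determine power, and its decision rule names the 95% CI.

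**Conclusion.** The point holds for the worked example and for the criterion it illustrates: failure to show non-inferiority is reported as inferiority. Under that criterion equal treatments would be labelled inferior with probability 1 − power, about 7% at 94 per group and 16% at 70 per group for each comparison. This assumes a 95% CI, an unadjusted two-sample t basis and a true d of 0; a gain in precision from ANCOVA would lower it.

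A reader might infer that the hub would be condemned in most trials, or that the trial's error rate or power is wrong because of this example. Neither follows. Once the non-inferiority criterion is read as an upper limit below 0.50, its type I error, power and sample size are untouched. What is wrong is the conclusion drawn when that criterion is not met.

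**What to change.** Replace both formal sentences and the second example with one rule for d = hub minus ICAU on scales where higher is worse:

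1. Non-inferior if the upper limit is below 0.50.
2. Inferior by the margin only if the lower limit is at or above 0.50.
3. Otherwise, non-inferiority not shown.

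Report separately whether the interval excludes 0. Restate the example with estimate 0.40 and limits 0.10 and 0.70 as non-inferiority not shown, with a difference favouring ICAU whose size relative to the margin is unresolved, and remove the stray minus sign.

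Make the change together with the correction of the reversed non-inferiority inequality, since all of these sentences stand in the same paragraph, and settle it before the allocation is unmasked. The cost is a wording change, with no effect on data collection or sample size.
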